### Outcomes

The primary outcome is the change in MoCA score from baseline to week 12. The secondary outcomes include the following: (1) the changes in STT, ADL, GDS, and DHI score from baseline to week 12; (2) new vascular events; and (3) the changes in serum level of homocysteine (Hcy), high-sensitivity C-reactive protein (HS-CRP), and D-dimer from baseline to week 4 and 12, respectively. The exploratory outcome is the changes in the Tinetti POMA score from baseline to week 12.

### Safety assessment

Safety assessment is performed at weeks 0, 4, and 12 by monitoring vital signs, general biochemical examinations, 12-lead electrocardiogram examinations, and the incidence of cardiovascular and cerebrovascular ischemia or bleeding events. All AEs observed by investigators or reported spontaneously by participants throughout the trial will be registered. For related to the trial, the investigators will give symptomatic treatment. Investigators will also collect the detailed characteristics of AEs, including reasons, grades, actions taken regarding AEs, dates of treatment initiation and end, and treatment outcomes. AEs are graded as mild, moderate, serious, life-threatening, and death. Serious AEs (SAEs) include death, a life-threatening AE, hospitalization or prolongation of hospitalization, a persistent or significant disability, a congenital anomaly, or a significant medical event that requires intervention. Any SAEs should be reported to the local Food and Drug Administration, National Medical Products Administration, and National Health and Family Planning Commission within 24 hours.

### Plans to promote participant retention and complete follow-up

Participants will receive extensive information about the study setup and requirements during the recruitment process. The importance of completing the follow-up will be stressed. The trial will maximize both enrollment and participant retention via multiple pathways, including collecting support system contact information during informed consent, appointment reminders, and support for transportation. Participants will be allowed to withdraw from treatment at any time. Participants who prematurely exit the study will still be encouraged to participate in regular follow-up visits, ensuring data will continue to be collected.

### Statistical analysis

The efficacy analysis is based on the intention-to-treat (ITT) population, which is defined as all randomized participants. All efficacy analysis results are analyzed in the full analysis set (FAS) and per-protocol set (PPS). The FAS is defined as all randomized patients who received at least one dose of the study drug and had both baseline and at least one post-baseline measurement of primary efficacy. The PPS is defined as all patients who completed the treatment without serious violation of the protocol. The safety analysis is performed in a safety set (SS), which is defined as participants who receive at least one dose of the study drug and at least one assessment of safety data. Categorical data will be expressed as numbers and percentages, and quantitative data will be expressed as means±SD, median, interquartile range (IQR) values, or minimum and maximum. For the primary outcome, the analysis of covariance (ANCOVA) will be performed to compare the 12-month MoCA outcomes (the change in MoCA score from baseline to week 12) between the groups at follow-up adjusting for baseline scores. For secondary and exploratory outcomes, the ANCOVA will also be performed to test for statistical differences between the groups. A repeated-measures analysis of variance (ANOVA) was performed to investigate the time-course of the changes in serum level of Hcy, HS-CRP, and D-dimer from baseline to weeks 4 and 12 within each group and to compare those between two groups. Pearson *χ*^2^ or Fisher’s exact test will be performed to compare differences in AEs of two groups. Any potential effects related to site differences will be assessed using mixed models. The baseline will be taken as the covariate in the model, and the effect of the center will be considered. In the case of missing data, we will capitalize on multiple imputation techniques to handle the issue of missing data in this study. All statistical analyses will be performed using Statistical Analysis System (SAS Institute, Inc, Gary, NC), and statistical significance was set at *p*<0.05.

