Withdrawal criteria from the treatment are as follows: (1) participants or their guardian withdraw informed consent; (2) participants lost to follow-up; (3) sensitivity to Dengyinnaotong Capsule or their components; (4) participants experience severe complications or deterioration during the trial period in which urgent measures were required; (5) participants become pregnant during the trial; and (6) other reasons. The reason for the participant being withdrawn from the trial will be recorded. If the participant is still willing to complete the follow-up, then the follow-up process will continue.

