### Sample size calculation

The sample size calculation is based on previous studies [14, 20, 21]. The routine basic treatment has been proved to improve the MOCA score of patients with CSVD by 2 points [20]. Besides, the routine basic treatment combined with Yinxingye is effective in the treatment of cognitive impairment in non-demented patients, with a MOCA score improved by 3 points [21]. Moreover, Wu et al. have found that Dengyinnaotong Capsule is better than Yinxingye Capsule in terms of effective rate and improvement symptoms in the treatment of ischemic stroke [14]. Therefore, based on the above results, we assume that the routine basic treatment combined with Dengyinnaotong Capsule in this trial will improve the MOCA score of patients with CSVD by 2 points compared with the routine basic treatment. Accordingly, 108 per group will be sufficient with a level of significance of 95% (*α*=0.05), a power of 90% (*β*=0.1), and an assumed standard deviation (SD) of 4.5. Considering the drop-out rate of 20%, a total of 270 samples (135 per group) are needed at least.

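### The full analysis set requires a post-baseline MoCA, and MoCA is measured after baseline only at week 12, so the set contradicts the stated ITT population and leaves no missing primary value to impute

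*Protocol article*

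**What the plan says.** The Statistical analysis section of the protocol article opens with "The efficacy analysis is based on the intention-to-treat (ITT) population, which is defined as all randomized participants". Its next sentence names other sets: "All efficacy analysis results are analyzed in the full analysis set (FAS) and per-protocol set (PPS"). The FAS is then restricted to "all randomized patients who received at least one dose of the study drug" who also "had both baseline and at least one post-baseline measurement of primary efficacy". The per-protocol set is limited to patients who completed treatment without a serious protocol violation. Later in the section, on missing data, it says "we will capitalize on multiple imputation techniques to handle the issue of missing data in this study", without naming the set to which this applies.

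Under Outcomes, "The primary outcome is the change in MoCA score from baseline to week 12". Table 1 (Data collection) marks MoCA at screening/baseline and at week 12; the week-4 cell is empty. Under Participants eligibility, the withdrawal criteria concern withdrawal from treatment, and the text adds: "If the participant is still willing to complete the follow-up, then the follow-up process will continue".

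**The concern.** A condition of one post-baseline measurement is mild when the endpoint is measured several times, because it then drops only participants with no follow-up data on that scale. Here there is one scheduled post-baseline MoCA, and it is the endpoint. The condition therefore means that the primary outcome was observed. Three things follow.

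- The FAS is not the ITT population named just before it, and no sentence assigns any analysis to all randomized participants.
- Membership depends on something that happens after randomization, in an open-label trial. If the arms differ in how many participants miss week 12, or in how those participants would have done, the FAS comparison is no longer the randomized one.
- Because all efficacy results use these sets, the filter reaches the secondary outcomes. A participant with a new vascular event, or with week-4 homocysteine, hs-CRP and D-dimer values, leaves the efficacy analysis if the week-12 MoCA is absent.

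**Working it through.** **1. The planned sample size.** Inputs from Sample size calculation: difference 2 points, SD 4.5, alpha 0.05 (taken as two-sided), power 90%, drop-out 20%.
- Normal approximation: n = 2 × (1.960 + 1.282)² × 4.5² / 2² = 106.4, so 107 per group.
- Exact t-test: power is 0.899 at 107 and 0.902 at 108, so 108 per group.
- Drop-out: 108 / (1 − 0.20) = 135 per group, 270 in total.

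The stated figures reproduce. The 20% allowance already provides 108 observed outcomes per group, so the required number does not depend on how the set is defined.

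**2. What the FAS condition means.** Scheduled post-baseline MoCA measurements (Table 1): 1, at week 12. Having at least one of one is the same as having the week-12 value. Missing primary values possible inside the FAS: 0.

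**3. How many are left out.** If every planned drop-out lacks a week-12 MoCA: 0.20 × 270 = 54 omitted, 216 kept (108 per group). Over an assumed 5% to 30% missing, 0.05 × 270 = 13.5 to 0.30 × 270 = 81 are omitted.

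**4. Possible bias.** Let p be the proportion in an arm without a week-12 MoCA, and d the shortfall in their MoCA change relative to those observed. The mean of the whole arm is the observed mean minus p·d. The observed difference therefore exceeds the all-randomized difference by

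p_E·d_E − p_C·d_C.

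This is zero whenever the two products are equal. The documents give neither arm-specific p nor any d. Under assumed values with the same shortfall of 1 to 3 points in both arms:

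| Missing, experimental vs control | Bias in points |
|---|---|
| 20% vs 20% | 0 |
| 25% vs 15% | 0.1 to 0.3 |
| 30% vs 10% | 0.2 to 0.6 |

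These show scale only; they are not estimates for this trial.

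**5. What imputation could repair.** Simulation under assumed conditions: 135 per arm, effect of 2 points in those observed, about 20% missing, imputation by arm from baseline MoCA alone.
- Missing participants do 2 points worse in the experimental arm only: all-randomized difference about 1.6, observed-case ANCOVA about 2.0, multiple imputation about 2.0.
- Missingness depends on baseline MoCA and arm: all three about 2.0.

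Imputing the endpoint from baseline alone thus gives nearly the same answer as the observed-case ANCOVA. A different answer must come from week-4 information or from explicit departures from missing-at-random.

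**The case against.** The best defence is that the section starts from all randomized participants and promises imputation for the study as a whole. One could read it as ITT with imputation for the primary analysis and FAS and per-protocol analyses alongside. That reading is possible, but the text does not state it: the only sets to which efficacy results are assigned are the FAS and the per-protocol set. The text supports two primary analyses, one of 270 participants and one of perhaps 216.

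Several stronger readings are tempting, and the documents do not support them.

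- *The FAS contains only participants who completed treatment.* The protocol continues follow-up after treatment stops, and the retention section encourages it. Someone who stops the capsule but attends week 12 stays in the FAS.
- *54 participants will be excluded.* That is the planning allowance, reached only if every drop-out lacks the week-12 MoCA.
- *Multiple imputation is disabled.* It is emptied only for the primary outcome within the FAS. It can still serve STT, ADL, GDS, DHI and the biomarkers.
- *The primary estimate is biased by a known amount.* Any figure needs assumed shortfalls. Nor is the bias zero only when the arms lose participants of equal prognosis; the condition is equality of the products p·d.
- *Vascular events disappear.* Ischemic and bleeding events are monitored under Safety assessment, and the safety set has no MoCA condition. They are lost from the efficacy analysis of a named secondary outcome, not from reporting.

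It is also fair that the trial is described as exploratory under Study design, and that imputation from baseline alone would change the estimate little. Both limit the likely size of the harm; neither removes the contradiction over who is analysed.

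**Conclusion.** The point holds as a contradiction between stated rules, not as missing detail. Read with Table 1, the FAS is the set with an observed week-12 MoCA. It conflicts with the ITT population, omits up to about 54 of 270 participants at the planned drop-out rate, and contains no missing primary value for the planned imputation. This rests only on the definitions and the MoCA schedule. The effect on the estimate is p_E·d_E − p_C·d_C, of unknown size and possibly zero.

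The same definition has a second defect. It requires a dose of study drug, yet under Intervention the control group receives routine treatment without the capsule. Read literally, no control would qualify. That is plainly not intended, but the wording needs correcting.

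**What to change.** 1. Define the primary efficacy set as all randomized participants, analysed as allocated, with no post-baseline condition and no dose condition.
2. Name one primary analysis: the baseline-adjusted ANCOVA of MoCA change to week 12 in that set. Multiply impute missing week-12 MoCA using arm, baseline MoCA and the week-4 data collected routinely (Table 1 has no week-4 MoCA, and week-4 STT is optional). Handle centre in a form that suits sparse cells: 270 / 25 / 2 = 5.4 participants per centre and arm.
3. Analyse new vascular events in all randomized participants, and keep the available week-4 biomarkers whether or not a week-12 MoCA exists.
4. Label the observed-week-12 and per-protocol analyses as sensitivity analyses.
5. Add a delta-adjusted (missing-not-at-random) sensitivity analysis, varying the shift separately by arm, because imputation under missing-at-random will stay close to the observed-case result.

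The cost is a little more programming and possibly a slightly wider interval; the sample size is unchanged. The change must be documented before database lock. The section on register, ethics and data management attaches approval and re-consent to any protocol change, so the sponsor should settle whether this is recorded as an amendment or in the SAP.

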### Intervention

Participants in the control group are treated with routine basic treatment. Participants in the experimental group are treated with routine basic treatment plus Dengyinnaotong Capsule (Kunming Pharmaceutical Group Co., Ltd., Yunnan, China; 0.52 g/time, 3 times/day). The routine basic treatment is performed according to the “Chinese Diagnosis and Treatment Guidelines for Cognitive Dysfunction Related to Cerebral Small Vascular Disease (2019)” and “Consensus on Diagnosis and Treatment of Cerebral Small Vascular Disease in China (2015)” [19]. The total treatment period is 12 weeks. If there are AEs during treatment, the investigators can decide whether to terminate or postpone the medication according to the severity. In addition, for other concomitant diseases, combined drugs can be used on the premise of not affecting the judgment of the efficacy of the test drugs. During the trial period, it is forbidden to use other Chinese medicines, including Chinese patent medicine, Chinese medicine injections, and Chinese medicine decoctions, decoction pieces, and formula granules.

During the trial, to ensure the compliance of participants, it is important for them to fully understand the significance of the trial, the importance of taking the medicine on time, and the necessity for follow-up. The subjects will be required to take the medicine according to the regulations, fill in the patient diary card on time, and attend the follow-up as required. In order to assess drug compliance, participants will be checked for the remaining number of drugs at each follow-up visit.

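### Read literally, the safety set and the FAS contain no controls, so the planned between-group comparison of adverse events cannot be run as defined

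*Protocol article*

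**What the plan says.** All four analysis sets are defined in the Statistical analysis section of the protocol article.

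- ITT: "The efficacy analysis is based on the intention-to-treat (ITT) population, which is defined as all randomized participants".
- FAS: "The FAS is defined as all randomized patients who received at least one dose of the study drug", who must also have a baseline and a post-baseline measurement of the primary efficacy variable.
- PPS: "The PPS is defined as all patients who completed the treatment without serious violation of the protocol".
- Safety set: "defined as participants who receive at least one dose of the study drug and at least one assessment of safety data".

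The section first bases efficacy on the ITT population, then says that all efficacy results are analyzed in the FAS and the PPS. For adverse events it plans a Pearson chi-square or Fisher's exact "test will be performed to compare differences in AEs of two groups".

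The Intervention section describes the arms. "Participants in the control group are treated with routine basic treatment", and the experimental arm receives the same plus Dengyinnaotong Capsule. No placebo is mentioned anywhere.

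**The concern.** Two of the four sets depend on a drug that one arm never receives. Efficacy and safety are both stated aims, and the safety assessment names ischemic and bleeding events, so the between-arm comparison of adverse events matters. A set that contains only capsule recipients cannot supply it.

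The analyst would then have to choose a workaround that the plan does not state. The obvious one is to apply the dose condition to the experimental arm only. That removes randomized participants from one side on the basis of something that happens after randomization. Participants and investigators know the allocation, so not starting the capsule may itself depend on the allocation.

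**Working it through.** **Inputs**

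- 135 per group, 270 in total (Sample size calculation), with 1:1 allocation (Randomization, allocation concealment, and blinding).
- The set definitions (Statistical analysis) and the arm definitions (Intervention).
- MoCA scheduled at baseline and week 12 only (Data collection, Table 1).
- Share of the experimental arm never dosed: not given. 2% to 5% is assumed here for illustration.

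**The plan's own figure.** For a difference of 2 points, SD 4.5, two-sided alpha 0.05 and power 0.90, the normal approximation gives n = 2 × (1.960 + 1.282)² × (4.5 / 2)² ≈ 106.4, so 107 per group. The t-test version gives 107.4, so 108, as stated. With 20% drop-out, 108 / (1 − 0.20) = 135 per group, or 270 in total. The sample size reproduces and is not at issue; 135 serves below only as the denominator.

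**Controls in each set if study drug means the capsule**

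| Set | Dose condition | Controls possible |
|---|---|---|
| ITT | none | up to 135 |
| FAS | yes | 0 |
| PPS | none (completion of treatment, no serious violation) | up to 135, less non-completers and serious violators |
| Safety set | yes | 0 |

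A two-group test of adverse events needs a count from each arm. In the safety set the control denominator is 0, so the test is undefined, and no other safety population is named. In the FAS the between-group ANCOVA fails for the same reason, but the ITT population and the PPS still allow it.

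**Condition applied to the capsule arm only.** Excluded experimental participants = 135 × share never dosed:

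- 2%: 135 × 0.02 = 2.7, about 3
- 5%: 135 × 0.05 = 6.75, about 7

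Excluded controls: 0.

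For the FAS these counts are upper bounds. The FAS also needs a post-baseline MoCA, which is scheduled only at week 12, so the dose condition removes someone extra only if that person was never dosed and still attended week 12. For the safety set the counts may apply nearly in full, because the Safety assessment section includes week 0 among its time points and a baseline assessment could satisfy the assessment condition.

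**The case against.** The strongest reply is that study drug simply means the allocated treatment, so the condition applies to both arms. The context gives this some support. The same section plans between-group analyses, the Discussion refers to dosing that differs between the two arms, and the Intervention section does not limit diary cards or counts of remaining drug to one arm. On that reading no control is lost for lack of the capsule.

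This shows what was probably intended, but it does not settle the rule. No passage defines the term that way, and the Intervention section uses *test drugs* for the product whose efficacy is being judged. Routine treatment is set by reference to guidelines, and the Background counts healthy lifestyle and risk-factor control among the main approaches. A control managed that way might have no first dose, while a control already on background drugs could meet the condition before randomization.

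A second reply is that safety sets are usually exposure-based, so leaving out never-exposed participants is ordinary. That is fair as a convention. Here, however, the condition can act on one arm only, and the participants know their arm.

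A third reply stands in full. A reader might infer that the trial has no control group for efficacy either. The documents do not support this, since the ITT population is all randomized participants and the PPS carries no capsule condition. Nor do they support an inference that adverse events are counted from different starting points in the two arms: the Safety assessment section registers all events throughout the trial.

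**Conclusion.** The point holds for the safety set and the FAS. Under the literal definitions, 0 of about 135 controls are in either. The consequence is most serious for safety, where no alternative population exists and the stated comparison cannot be carried out. For efficacy it is confined to the FAS, although the section does not make clear whether the ITT population or the FAS takes precedence.

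This is a stated rule that does not fit an add-on design without placebo. It is not a detail that can be presumed left to an analysis plan.

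The one-sided exclusion is a secondary issue of unknown size. The figure of about 3-7 of 135 rests wholly on the assumed 2-5% never dosed and is an upper bound for the FAS. No bias in the MoCA difference or in event rates has been derived from it. The sample size is unaffected.

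**What to change.** Before database lock, reword two definitions.

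1. **Safety set:** all randomized participants with at least one post-randomization safety assessment, the same rule in both arms, compared by allocated arm. Add an as-exposed summary for those who took at least one capsule, as a supplement.
2. **FAS:** delete the dose condition, so that the set applies equally to both arms and agrees with the stated ITT basis.

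Grouping by treatment received should not be the main safety comparison. Counting everyone without a capsule as a control would move never-dosed experimental participants into the control arm, with practically no movement the other way, which replaces a one-sided exclusion with a one-sided reassignment.

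The cost is wording only: no new data, visits or participants. With all participants eligible, each set can hold up to 135 + 135 = 270. The downside is that never-dosed experimental participants stay in the experimental arm and may slightly dilute its adverse event rates; the as-exposed summary is there to show this.

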### Randomization, allocation concealment, and blinding

All eligible participants are randomly assigned to an experimental group (routine basic treatment plus Dengyinnaotong Capsule) or control group (routine basic treatment) in a ratio of 1:1. The simple randomization is generated centrally by the trial biostatistician using a computer-generated random number table. A central, web-based system will provide a unique trial identifier for each participant via email to a delegated member of site staff. Due to the open-label design, the participant, investigator, and project management teams are aware of the treatment allocation.

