### Data collection

In this trial, data collection will be performed at weeks 0, 4, and 12 in the treatment period. The schedule of data collection is shown in Table 1. General biochemical examinations include blood routine, urine routine, stool routine, coagulation function, liver function, renal function, blood glucose, and blood lipid examination.

**Table 1 Tab1:** Schedule of data collection

Visits	Screening and baseline	Treatment period	
	0	1	2
Time points (weeks)	− 1 to 0	4	12
Time windows (days)	-	±7	±7
Informed consent	×		
Inclusion and exclusion criteria	×		
History of diagnosis and treatment	×		
Vital signs and physical examinations	×	×	×
General biochemical examinations	×	×	×
12-lead electrocardiogram examination	×	×^a^	×
CT or MRI examination	×	×^a^	×^a^
MoCA score	×		×
CDR score	×		×
Shape Trail Test	×	×^a^	×
ADL score	×		×
DHI score	×^a^	×^a^	×^a^
Tinetti POMA score	×^a^	×^a^	×^a^
GDS score	×^a^	×^a^	×^a^
Serum levels of Hcy, HS-CRP, and D-dimer	×	×	×
Audiological examination	×^a^	×^a^	×^a^
Drug combination	×	×	×

*MoCA* Montreal Cognitive Assessment, *CDR* Clinical Dementia Rating, *CT* Computed tomography, *MRI* Magnetic resonance imaging, *ADL* Activities Of Daily Living, *DH* Dizziness Handicap Inventory, *Tinetti POMA* Tinetti performance-oriented mobility assessment, *GDS* Geriatric Depression Scale, *Hcy* homocysteine, *HS-CRP* High-sensitivity C-reactive protein

^a^For patients with relevant clinical manifestations or willing to be examined

The 30-item clinician-administered MoCA is a brief cognitive screening tool with high sensitivity for screening patients with mild cognitive impairment [22]. It is a simple 10-min paper-and-pencil test that assesses multiple cognitive domains including memory, attention, concentration, language, visuospatial skills, abstraction, calculation, executive functions, and orientation.

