Despite the above strengths, there are still some limitations in the present study. Firstly, due to the different administration dosages of the two groups, the trial is openly labeled. The lack of blinding has the risk of both performance and detection bias. For example, patients or investigators might add concomitant treatments to address insufficient efficacy or manage symptoms or risk based on their beliefs and knowledge about treatment allocation. Secondly, although the vascular cognitive impairment is a gradual process from normal cognitive status to mild cognitive impairment and then dementia, this study only assesses the 12-week treatment outcome and does not seek to assess the long-term efficacy considering the poor compliance among elderly patients. Finally, we only evaluated the efficacy and safety of Dengyinnaotong Capsule on cognitive function related to CSVD at the specific dose. Dose-exploration study should be carried out in the further to determine the optimal dose of Dengyinnaotong Capsule for treating mild cognitive impairment related to CSVD.

In summary, the present trial is the first to investigate the efficacy and safety of Dengyinnaotong Capsule on cognitive function in patients with CSVD. The findings of this study might provide convincing evidence regarding the efficacy of Dengyinnaotong Capsule on mild cognitive impairment related to CSVD.

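### The blanket ANCOVA rule covers new vascular events, which have no baseline value, and the FAS and PPS can exclude a patient because of the event itself

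*Protocol article*

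**What the plan says.** The Outcomes section lists three kinds of secondary outcome. The first and third are changes from baseline in scales and serum markers. The second is "2) new vascular events", which is not worded as a change.

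The Statistical analysis section gives one rule for all of them: "For secondary and exploratory outcomes, the ANCOVA will also be performed to test for statistical differences between the groups". It adds: "The baseline will be taken as the covariate in the model, and the effect of the center will be considered". A Pearson chi-square or Fisher's exact "test will be performed to compare differences in AEs of two groups"; no categorical method is named for a secondary outcome.

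On populations, the same section bases efficacy on an ITT population of everyone randomized. It then says that all efficacy results are analysed in the FAS and PPS. The FAS needs a baseline and at least one later measurement of the primary efficacy variable. The PPS needs completed treatment.

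The Safety assessment section also monitors "the incidence of cardiovascular and cerebrovascular ischemia or bleeding events". In Table 1, CT or MRI is scheduled for everyone at screening and baseline, but at weeks 4 and 12 it carries the footnote "For patients with relevant clinical manifestations or willing to be examined".

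**The concern.** ANCOVA on change scores suits the scales and serum markers. It does not suit an event that by definition has not happened at baseline: there is no value to enter as covariate, and the output is a difference in adjusted means where a risk comparison is needed. The text fixes a method that does not fit the outcome, so this is more than detail left to an analysis plan.

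The analysis sets add a second problem. Eligibility for the FAS depends on a later MoCA, and eligibility for the PPS depends on finishing treatment. A vascular event can prevent either, so having the outcome can remove the patient from the analysis of that outcome. At stake is the plan's only clinical-event efficacy outcome, and whether its efficacy and safety tabulations agree.

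**Working it through.** **The plan's own figure.** Inputs from Sample size calculation: difference 2, SD 4.5, α 0.05 (taken as two-sided), power 0.90, drop-out 20%. The normal approximation gives n = 2 × (1.960 + 1.282)² × 4.5² / 2² = 106.4, so 107 per group. The t-test needs 108 (power 0.9017, against 0.8990 at 107). Then 108 / 0.80 = 135 per group, 270 in total. The figure reproduces. It concerns MoCA only, and supplies the 135 per arm used below.

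**Outcome against method.**

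| Outcome | Baseline value? | Method by the text | Fits? |
|---|---|---|---|
| STT, ADL, GDS, DHI change | Yes (Table 1) | ANCOVA | Yes |
| Hcy, HS-CRP, D-dimer change | Yes | ANCOVA and repeated-measures ANOVA | A baseline exists |
| New vascular events | None | ANCOVA with baseline covariate | No |
| Ischemia or bleeding events, as AEs | Not needed | Chi-square or Fisher, safety set | Yes |

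The same stroke could therefore be tested by two methods on two denominators, and nothing says which governs.

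**Does the wrong model give false positives?** Without the undefined covariate, ANCOVA on 0/1 data is a t-test. With a and b events in m per arm, x = a/m and y = b/m, t = (x − y) / √(2s²/m), where s² = [a(1 − x) + b(1 − y)] / (2m − 2). Exact two-sided size at m = 135, on assumed event rates:

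| True rate | Linear model | Pearson | Fisher |
|---|---|---|---|
| 0.5% | 0.0050 | 0.0050 | 0.0001 |
| 1% | 0.0247 | 0.0247 | 0.0013 |
| 2% | 0.0453 | 0.0453 | 0.0096 |
| 3% | 0.0437 | 0.0437 | 0.0169 |
| 5% | 0.0479 | 0.0479 | 0.0227 |

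The linear model matches Pearson to four decimals and never exceeds 0.05.

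**Who leaves the analysis sets.** Table 1 schedules MoCA at screening/baseline and week 12 only. A patient who has an event and dies or is lost before week 12 has no later MoCA and is outside the FAS, although the event was observed. The withdrawal criteria include serious complications or worsening that need urgent action, so a patient with an event may stop treatment and leave the PPS even if followed to week 12.

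**Size.** Expected events per arm at assumed rates: 135 × 0.01 = 1.35; 135 × 0.05 = 6.75. Illustration: 3 events in each arm of 135 gives a risk difference of 0 and a ratio of 1.0. If one control patient with an event is lost before week 12, and only that patient is excluded, the FAS shows 3/135 = 2.22% against 2/134 = 1.49%, a difference of 0.73 percentage points and a ratio of 1.49. Fisher's p is 1.0 both times: the estimate moves, the test result does not.

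**Conditional: if scan findings count.** Assume 2% of patients have clinically evident events, always found; 3% to 10% have silent events, found only if scanned; and scan uptake is 30% in one arm and 60% in the other, with no true effect.
- 3% silent: (0.02 + 0.03 × 0.3) / (0.02 + 0.03 × 0.6) = 0.029 / 0.038 = 0.76
- 5% silent: 0.035 / 0.050 = 0.70
- 10% silent: 0.050 / 0.080 = 0.63

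With uptake reversed the ratios are 1.31, 1.43 and 1.60. With equal uptake the ratio is 1.0.

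**The case against.** **The ITT sentence.** The section opens by basing efficacy on all randomized participants, and it plans multiple imputation. That is a fair counterweight, but the next sentence sends every efficacy result to the FAS and PPS, and the text does not say which set governs. Imputation does not help a patient whom the set definition excludes.

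**Follow-up after withdrawal.** Willing participants are followed after stopping treatment, so stopping does not by itself remove anyone from the FAS. This stands. The FAS problem is confined to death or loss before week 12; the PPS problem is wider.

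**The safety analysis.** Much the same events will probably also be compared as AEs by chi-square or Fisher, in a set that needs no week-12 MoCA. This stands and limits the harm. It also leaves two methods and two denominators for overlapping events.

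**No inflated type I error.** A reader might infer that ANCOVA on event data produces false positives. The calculation above does not support that.

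**Imaging.** A reader might infer that new vascular events are partly found by the optional scans, so that scan uptake alone could make the drug look protective or harmful. The protocol article does not say that follow-up CT or MRI feeds this outcome or that silent lesions count, and a condensed article may leave the event definition to the full protocol. What stands is conditional. The text says that "the participant, investigator, and project management teams are aware of the treatment allocation" and concedes in general terms that "The lack of blinding has the risk of both performance and detection bias". If scan findings count, detection could differ by arm.

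**Conclusion.** The point holds on two counts. First, the stated rule assigns new vascular events a model that needs a baseline value they do not have and that reports an unsuitable effect measure, while overlapping safety events get a different test in a different set. Second, the FAS and PPS definitions can exclude a patient because of the event, and the ITT sentence does not resolve this.

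The size is modest. This is a secondary outcome in a trial described as exploratory, and with about 1 to 7 events per arm (assumed rates of 1% to 5%; the document gives none) one excluded event shifts the estimate visibly without changing a test result. The harm lies in the model, the effect measure and the outcome-dependent exclusion. The imaging point is a question for the sponsor, since the documents do not show that scan findings enter the outcome; for the same reason they give no basis for redefining the outcome as clinically manifest events only.

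**What to change.** - Restrict the ANCOVA sentence to the continuous change scores and serum markers.
- Analyse new vascular events in all randomized participants: number and proportion with at least one event per arm, Fisher's exact test, and a risk difference with 95% CI. Fisher's test is conservative at these counts, so the interval should carry the interpretation.
- Align this with the safety analysis of the same events, so that any difference in counts or denominators is intended and explained.
- State whether findings on the optional week 4 and week 12 CT or MRI count as events. If they do, report scan-only findings separately, with the number scanned per arm.

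The cost is wording in the protocol or analysis plan, settled before database lock. No new data are needed: adverse events are recorded throughout the trial, and willing participants are followed after stopping treatment.
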